### Concomitant medications

No new medications that could affect BP will be introduced for the duration of this study. Subjects should not take any traditional medicine for at least 2 weeks prior to commencing the study, and throughout the conduct of the study. During the study, subjects are advised not to take any other antihypertensive medications other than medications(s) that they were taking at the start of the study. If concomitant medication is unavoidable in case of emergency, the use must be reported in the patient’s diary (comment log) (dose and time of administration) and possible effects on the study outcome must be addressed (see also “Study withdrawal or interruption”). All other medicines that the patient takes will remain constant for the duration of the equivalence test.

### Education and instruction for subjects

To be included, participants should be able to demonstrate that they can measure and record their BP appropriately. Before randomization, each eligible participant will be trained using a standardized protocol for home BP measurement. Subjects will be trained about the basic methods of BP self-measurement, the meaning of BP values, and the monitoring device to be used by the principal investigator and study physician. Each patient will be given a digital home BP monitor. Subjects will be instructed to measure their BP three consecutive times in the sitting position in the morning before breakfast and in the evening after dinner. They will also be asked to visit the study site for follow-up on a weekly basis. They will be asked to take the respective study medication in the sitting position together with 250 ml water at the same time each day.

### Sample size estimation

The sample size for the individual N-of-1 trial is 30 BP readings (twice a day, three times each time) taken from the last 5 days of each trial period. The selection of a 5-day period of usable data in our study, and the number of BP readings required to sufficiently determine whether the local enalapril is therapeutically equivalent or not, is based on a previous N-of-1 trial of enalapril by Chatellier et al. [23]. Their investigation included two successive studies. In study 1, the variance components of BP and the choice of treatment period duration were determined in 35 hypertensive patients who remained untreated during the measurements. In study 2, a series of individual N-of-1 trials of identical design was performed after study 1 completion in 44 other consecutive patients. The first phase of the study reported that a period of five consecutive days of BP measurement is sufficient to accurately detect a drug-induced fall in BP in a single patient, provided that there are at least 30 readings in each 5-day trial period. However, the study did not consider the washout period and the individual agreement between the two cycles was only moderate at best. The authors recommended a trial of longer periods with three cycles. The 5-day period is a compromise between acceptability of the length of the individual trial and the reduction of variance allowed by the repetition of measurements with time.

An audit of sample sizes for pilot and feasibility trials undertaken in the United Kingdom reported that the median sample size for pilot trials was 30 participants per arm [30]. We assume that a sample size of 30 patients is adequate to assess feasibility. Considering a 10% dropout, a total of 33 participants will be included in the study. Only 10% dropout was considered based on the low dropout rate history from a previous cholera trial [31].

### Outcome measures

The study physician will assess the patient before and after each treatment period (each week) and collect home BP measurement and Side-effect Recording Forms from the previous week.

### Primary outcome

Therapeutic equivalence will be assessed by calculating change in mean seated systolic blood pressure (SBP). The minimal clinically important difference (MCID) is the smallest treatment effect that would lead to a change in a patient’s management [32]. Based on the academic literature [33], an average SBP difference of 5 mmHg is accepted as the MCID. A difference of < 5 mmHg in SBP between the two treatments is, therefore, considered to be of no clinical importance. Clinically important differences can be defined using a predefined MCID and confidence interval of the difference of the two treatments [34].

Clinically important differences in mean BP readings between the two treatments can have four interpretations, depending on the relationship of the MCID of the intervention to the point estimate (the best single value of the efficacy of the intervention that has been derived from the study results) and the 95% CI surrounding it [34] (see Fig. 4):

**Fig. 4 Fig4:**
[figure not shown]
Mean clinical difference between two treatments (mean systolic blood pressure (BP)).  point estimate of the difference between groups,  95% confidence intervals, *minimum clinically important difference (MCID)

Definite – when the MCID is smaller than the lower limit of the 95% CIProbable – when the MCID is greater than the lower limit of the 95% CI, but smaller than the point estimate of the efficacy of the interventionPossible – when the MCID is less than the upper limit of the 95% CI, but greater than the point estimate of the efficacy of the intervention, andDefinitely not – when the MCID is greater than the upper limit of the 95% CI

### Criteria to establish therapeutic equivalence

Absence of a clinically important difference – for therapies to be considered equivalent, not only should the comparison of the efficacies of the two interventions not reach statistical significance, but also the upper limit of the confidence interval should be smaller than the predetermined MCIDEquivalence should be evident in at least in two cycles out of three

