#### Statistical methods

Analysis will be conducted based on BP measurements taken in the last 5 days of each of the six periods. The first 2 days’ BP measurements in each period will be discarded. Based on the academic literature [33], 6 mmHg is accepted as the MCID. Therefore, a SBP difference of ≥ 5 is considered clinically significant. A mean change in evening SBP of < 5 mmHg between the two test medicines in at least two treatment cycles will be considered as representing TE.

Differences in treatment means will be explored graphically, and through the paired Student’s *t* test as appropriate. Significance will be set at *P* < 0.05. The data will also be modeled within a linear mixed-effects modeling framework to account for repeated measures over time such that between- and within-patient variability can be captured (and estimated). If the modeling provides evidence that sources of variability are significant (e.g., possible relationships between the three readings at each morning and evening), then appropriate adjustments built in to the model will be retained. From such a model, population and individual estimates of treatment means can be obtained, and the influence of additional variables. such as treatment order. can be accounted for (if needed). This statistical analysis will be undertaken in the R package.

The type and severity of possible side effects of the study medication and any serious adverse events will be tabulated for individual patients.

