## Discussion

The numbers of local pharmaceutical industries that market their products, such as enalapril, without proof of bioequivalence are dramatically increasing. The Ethiopian guideline for registration of medicines states the need for clinical trial evidence on occasions when PK bioequivalence is not applicable. The guideline states that when in-vivo studies using plasma concentration time-profile data are not suitable, a comparative clinical trial then has to be performed to demonstrate equivalence between two formulations. However, as stated in the background, in East Africa including Ethiopia, local generics are marketed without evidence of effectiveness obtained through bioequivalence studies or clinical trials.

By bridging the information gap on bioequivalence, the trial will give rigorous evidence on TE of local enalapril in individual patients. If there is no difference between the two treatments (the hypothesized result), then patients can take the local cheaper medicine with confidence. This trial will also will determine whether aggregated N-of-1 studies are feasible to provide a population level estimate of clinical equivalence for untested generic drugs in resource-limited countries where bioequivalence testing centers are unavailable. If TE is shown, it will encourage the use of cheaper local drugs by enhancing reliance on local pharmaceutical companies.

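### The therapeutic-equivalence rule fails precise differences that lie wholly inside ±5 mmHg because it demands non-significance, and it checks one confidence limit of a difference whose direction is undefined

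*Protocol article*

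**What the plan says.** All references are to the protocol article.

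- *Criteria to establish therapeutic equivalence* asks that the comparison of "the two interventions not reach statistical significance, but also the upper limit of the confidence interval should be smaller than the predetermined" MCID, and that this be seen in two or more of the three cycles. It sets no condition on the lower limit.
- *Primary outcome* sets the margin: "an average SBP difference of 5 mmHg is accepted as the MCID". It adds: "A difference of < 5 mmHg in SBP between the two treatments is, therefore, considered to be of no clinical importance". Neither statement has a direction. Results are to be read from the point estimate and "the 95% CI surrounding it".
- In the four-category scheme that accompanies Fig. 4, a clinically important difference is ruled out (*Definitely not*) "when the MCID is greater than the upper limit of the 95% CI". Only the upper limit is used here too.
- *Statistical methods* says "Significance will be set at *P* < 0.05", without stating sidedness. It also says "6 mmHg is accepted as the MCID", then treats 5 mmHg or more as clinically significant. It gives a separate TE rule: an evening SBP difference under 5 mmHg in two or more cycles, with no interval and no test.

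No section says which product's mean is subtracted from which.

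**The concern.** Equivalence within a margin is a statement about where the whole confidence interval lies: both limits must fall between -MCID and +MCID. The stated criterion departs from this in two ways.

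1. **Non-significance is required.** An interval can lie wholly inside the margin and still exclude zero. The criterion then denies TE to a difference that *Primary outcome* calls unimportant. The better the data, the more often this happens.
2. **Only one limit is checked, and the sign is undefined.** If the difference is signed, nothing stops the interval from reaching far below -MCID.

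The stakes are the trial's statement on TE and the individual results, which go to treating physicians for a decision about the local drug (*Individual study result report*).

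**Working it through.** **Inputs.** Margin 5 mmHg (*Primary outcome*). 95% CI (*Primary outcome*). P < 0.05 (*Statistical methods*), taken as two-sided to match the CI. The protocol gives no SD, power or type I error for the TE criterion, so there is no figure of its own to reproduce. Its total of 33 patients (30 × 1.10) is justified by feasibility and does not bear on this rule. The SEs below are assumptions.

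**Model.** The estimate d is normal around the true difference with standard error SE.

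- Stated rule, signed: |d| ≤ 1.96·SE and d + 1.96·SE < 5.
- Two-limit rule: |d| < 5 - 1.96·SE.

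**Part 1: the non-significance condition.**

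A CI of +0.1 to +3.9 has d = 2.0 and half-width 1.9. Both limits are inside ±5, but zero is excluded, so TE fails.

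True difference 2, SE 1:
- Stated rule: d must lie between -1.96 and 1.96. Φ((1.96 - 2)/1) = Φ(-0.04) = 48%; the lower tail is negligible.
- Two-limit rule: |d| < 3.04. Φ((3.04 - 2)/1) = Φ(1.04) = 85%.

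True difference 2, SE 0.75:
- Stated rule: d must lie between -1.47 and 1.47. Φ((1.47 - 2)/0.75) = Φ(-0.71) = 24%.
- Two-limit rule: |d| < 3.53. Φ((3.53 - 2)/0.75) = Φ(2.04) = 98%.

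At a true difference of 1 mmHg, acceptance under the stated rule falls as precision improves: 83% at SE 1, 48% at SE 0.5, 8.5% at SE 0.3. The two-limit rule gives 98%, 100% and 100%.

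Where this bites: an interval that is inside ±5 and excludes zero must have half-width below 2.5, so SE below 2.5/1.96 = 1.28. For a pooled estimate from 30 patients, an assumed SD of patient differences of 2 to 8 mmHg gives SE = SD/√30 = 0.37 to 1.46, mostly in that range.

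**Part 2: one limit, undefined sign.**

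A CI of -12 to +4 contains zero and has an upper limit below 5, so it passes if read as signed.

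True difference -6, SE 3: 1.96·SE = 5.88, so d must lie between -5.88 and 5 - 5.88 = -0.88. Φ((-0.88 + 6)/3) - Φ((-5.88 + 6)/3) = Φ(1.71) - Φ(0.04) = 0.956 - 0.516 = 44%.

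If the difference is always oriented positive, the upper-limit condition becomes |d| + 1.96·SE < 5. That is the two-limit rule, and acceptance here is 0%. The 48% and 24% in Part 1 do not change.

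SE 3 is plausible for one patient's single cycle. With 30 independent readings per period, SE = SD·√(2/30), which is 2.07 to 3.10 for an assumed reading SD of 8 to 12 mmHg, and more if readings are correlated.

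**Two of three cycles.** If cycles are independent, the chance is 3p² - 2p³. Then 48% becomes 48%, 24% becomes 14% and 44% becomes 41%. The cycle rule repairs neither part.

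**Limit of the two-limit rule.** It can pass only if 1.96·SE < 5, that is SE < 2.55. At SE 3 it accepts 0% even when the products are identical; the stated signed rule then accepts 36%.

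**The case against.** **The difference may be meant as positive.** The four categories compare a positive MCID with the lower limit, the point estimate and the upper limit of the intervention's efficacy. That ladder is coherent if the difference is oriented positive, and Fig. 4, which might settle it, is not shown here. Under that reading Part 2 vanishes. This stands: a reader might infer that the plan certainly passes large, imprecise differences as equivalent, and the documents do not support that. They leave the direction open, which is itself a gap in a decision rule. Part 1 is untouched.

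**Non-significance is not taken as proof.** The two conditions are joined, so non-significance alone never yields TE, and the clause can only make TE harder to declare. That is correct. The fault is false rejection, not false acceptance.

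**No error rate is stated.** A reader might set the 44% against an intended 2.5%. The protocol states no type I error for equivalence; 2.5% is merely what a two-limit 95% rule would give at the margin. Nor is 44% against 0% a fair contrast by itself, since at SE 3 the two-limit rule passes nothing at all.

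**This may not be the operative rule.** *Statistical methods* gives a different TE rule, and no section explicitly applies the criterion to the pooled estimate. So one cannot say that this criterion alone decides the trial's conclusion. The conflict is a further reason to rewrite it.

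**Conclusion.** The TE criterion is wrong as written because it requires a non-significant difference. This holds under any sign convention and contradicts the protocol's own statement that differences under 5 mmHg are unimportant. In the examples it cuts acceptance of a true 2 mmHg difference from 85% to 48% (SE 1) and from 98% to 24% (SE 0.75), per comparison and before the cycle rule. These figures rest on a normal model, a 5 mmHg margin and assumed SEs. The effect arises only at SE below about 1.28, so chiefly for pooled or otherwise precise estimates.

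The missing lower-limit check is a conditional fault. It is real if the difference is signed (44% acceptance at a true -6 mmHg, SE 3) and absent if the difference is always oriented positive. The protocol needs to say which applies.

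**What to change.** 1. Delete the non-significance condition from *Criteria to establish therapeutic equivalence*.
2. Define the difference as local minus imported.
3. Declare TE only if both limits of the two-sided CI (95%, as in *Primary outcome*) lie within -MCID to +MCID.
4. Rewrite the four Fig. 4 categories symmetrically for both directions.
5. Reconcile this with *Statistical methods*, so that one TE rule and one margin remain in place of the separate evening-SBP rule without an interval and the 5 versus 6 mmHg MCID.

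The cost is rewording of these sections and any matching text in the analysis plan; no new data are needed. The downside should be stated openly: with a 5 mmHg margin, a per-patient or per-cycle comparison with SE of about 2.55 mmHg or more can never meet the two-limit 95% rule. Such results should be reported as inconclusive.

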### Secondary outcomes

Change in mean home diastolic blood pressure (DBP) for both evening and morning diastolic BP valuesChange in mean clinic DBPChange in mean clinic SBPChange in mean home DBP measured in the morning, 24 h after drug intakeChange in mean home DBP measured in the evening, 12 h after drug intakeChange in mean home SBP measured in the evening, 12 h after drug intakeChange in mean home SBP measured in the morning, 24 h after drug intake
*Feasibility outcome*: based on the academic literature [35], the following criteria will be used to measure success/acceptability of the pilot study:Recruitment rate: at least 70% of all eligible patients can be recruitedCompletion rate: at least 80% of all recruited subjects complete the studyAt least 90% of patients took every scheduled dose of the study drug, andMore than 80% of requested measurements are obtained and valid. Measurements are considered invalid when either or both of systolic and diastolic BP readings are not compatible (less than 20 mmHg difference)Patients’ and physicians’ views on the trial

*Safety outcomes*: adverse events (AEs) (number, severity) identified by patients recording. AEs recorded by the physician on the AE Case Report Form (CRF)

### Establishing controlled BP

In this study, those with an average clinic BP measurement controlled at 140/90 mmHg or less for up to 12 months will be included. This is because there is a considerable placebo effect for antihypertensive medicines, which increases after 1 year [36]. Hypertensive patients who have their follow-up in the ALERT hospital usually have a monthly visit schedule. To account for BP variations, including seasonal ones, BP will be established by taking the average of three consecutive BP measurements taken in at least the last 2 months.

### Using home BP measurement

BP self-measurement at home has been shown to be a sensitive tool, able to detect small changes, frequently resulting in reduced variability and greater reproducibility of measurements compared to office BP readings [37, 38]. Blood pressure self-measurement eliminates the white-coat effect [39]. It also provides better prediction of organ damage than clinic BP measurement [40, 41] and reduces the number of subjects necessary for meaningful results in drug trials [42, 43]. The average systolic BP over 5 days is used to assess the effectiveness of treatment. Frequent measurement of BP over 5 days narrows the variability of BP around the true mean BP value [44].^.^ Frequent measurement of BP improves diagnostic and management capacity [45, 46]. Blood pressure should be recorded immediately in a study diary.

### BP self-monitoring device

A clinically validated digital BP machine will be used for home blood measurement. A home BP measurement protocol is developed using standard methodology [47]. Before use by patients, the accuracy of each machine will be verified at the clinic/trial center.

### Safety evaluation and monitoring

Because this is a study of medication that the patient has been taking, the risk of serious adverse events is minimal. All abnormal or unpleasant effects from medications will be considered as side effects. Individual patients will collect common side effects using a questionnaire at home and bring it during their weekly visits. If a patient develops a serious side effect, the study physician will take appropriate measures. The most common side effects of enalapril include increased serum creatinine (20%), dizziness (2–8%), low BP (1–7%), syncope (2%) and dry cough (1–2%). The most serious common AE is angioedema (swelling) (0.68%) which often affects the face and lips, endangering the patient’s airway.

The DSMB consists of two senior members with clinical and methodological expertise who are independent of the trial. They will review all documented harms during the study and adjudicate them with regard to causality.

### Study withdrawal or interruption

If a concomitant medication has to be taken that might influence BP, that person will cease the trial until the new medicine has ceased or the dose has been stable for at least 2 weeks. If they wish, the participant can restart the study, substituting a new randomly packed cycle of medicines for the interrupted cycle. Unused medicines from the trial will be discarded. If the person has to continue on the new medicine, the trial will cease, and the data collected will be analyzed if at least one cycle has been completed.

Participants will also be withdrawn from the study under the following conditions:Patient request, patient non-compliance, or the development of an exclusion criterionIf, in the opinion of the treating clinician, the patient’s interests are best served by withdrawing from the trial

### Data analysis and study result report

#### Individual study result report

At the end of the trial, BP measurements will be analyzed and the result will be given to the treating physician. After looking at these results, the patient and the treating physician will be able to decide if the local drug works for treating the patient’s hypertension.

#### Statistical methods

Analysis will be conducted based on BP measurements taken in the last 5 days of each of the six periods. The first 2 days’ BP measurements in each period will be discarded. Based on the academic literature [33], 6 mmHg is accepted as the MCID. Therefore, a SBP difference of ≥ 5 is considered clinically significant. A mean change in evening SBP of < 5 mmHg between the two test medicines in at least two treatment cycles will be considered as representing TE.

Differences in treatment means will be explored graphically, and through the paired Student’s *t* test as appropriate. Significance will be set at *P* < 0.05. The data will also be modeled within a linear mixed-effects modeling framework to account for repeated measures over time such that between- and within-patient variability can be captured (and estimated). If the modeling provides evidence that sources of variability are significant (e.g., possible relationships between the three readings at each morning and evening), then appropriate adjustments built in to the model will be retained. From such a model, population and individual estimates of treatment means can be obtained, and the influence of additional variables. such as treatment order. can be accounted for (if needed). This statistical analysis will be undertaken in the R package.

The type and severity of possible side effects of the study medication and any serious adverse events will be tabulated for individual patients.

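### The MCID that serves as the equivalence margin is 5 mmHg in one section and 6 mmHg in another, both citing the same reference

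*Protocol article*

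**What the plan says.** The Primary outcome section of the protocol article cites reference [33] and states that "an average SBP difference of 5 mmHg is accepted as the MCID". It then draws the consequence: "A difference of < 5 mmHg in SBP between the two treatments is, therefore, considered to be of no clinical importance".

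The Statistical methods section cites the same reference and states that "6 mmHg is accepted as the MCID". The next sentence reads: "Therefore, a SBP difference of ≥ 5 is considered clinically significant". The section's own equivalence rule follows, and it also uses 5: "A mean change in evening SBP of < 5 mmHg between the two test medicines in at least two treatment cycles".

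The section on criteria to establish therapeutic equivalence sets two joint conditions. The comparison must not be statistically significant, and "the upper limit of the confidence interval should be smaller than the predetermined" MCID. No figure is repeated there. The four categories listed under Fig. 4 (definite, probable, possible, definitely not) are likewise defined by where the MCID falls relative to the point estimate and the 95% CI.

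**The concern.** One reference is given two values, and the Statistical methods section is also inconsistent within itself: a cut-off of ≥ 5 does not follow from an MCID of 6. A difference of 5.5 mmHg would be below the MCID and clinically significant at once.

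The MCID is more than background here, because the equivalence criterion makes it the margin for the upper confidence limit. With two values in the text, some results would be equivalent or not depending on which section is followed, and that choice could be made after the interval has been seen.

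**Working it through.** **The plan's own figures.** The only derived sample size is 30 × 1.10 = 33, which reproduces the stated 33 participants. It rests on feasibility and a 10% dropout allowance. The readings per period, 5 days × 2 sessions × 3 readings = 30, also agree. Neither figure uses the MCID, so neither changes with 5 or 6.

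**Inputs.**
- Margin M = 5 (Primary outcome) or 6 (Statistical methods).
- 95% CI (categories under Fig. 4) and significance at P < 0.05 (Statistical methods).
- SE of the mean difference: not in the documents, so assumed, from 1 to 2.5 mmHg.
- Further assumptions: normal approximation, a two-sided test using the same SE as the CI, and the margin applied in both directions (95% CI within ±M).

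**Rule with both conditions.** Non-significance requires |estimate| < 1.96·SE. A CI within ±M requires |estimate| < M − 1.96·SE. Equivalence therefore requires |estimate| < c, where

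c = min(1.96·SE, M − 1.96·SE).

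For a true difference d,

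P(TE) = Φ((c − d)/SE) − Φ((−c − d)/SE).

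**Where the margin starts to matter.** With M = 5 the two limits cross at 1.96·SE = 5 − 1.96·SE, so SE = 5/3.92 = 1.28. Below that, non-significance is the tighter limit under either margin, and the decision is the same.

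**Results (margin 5 vs margin 6).**

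| Assumed SE | c | d = 0 | d = 4 | d = 5 |
|---|---|---|---|---|
| 1.0 | 1.96 vs 1.96 | 95% vs 95% | 2.1% vs 2.1% | 0.12% vs 0.12% |
| 1.5 | 2.06 vs 2.94 | 83% vs 95% | 9.8% vs 24% | 2.5% vs 8.5% |
| 2.0 | 1.08 vs 2.08 | 41% vs 70% | 6.7% vs 16.7% | 2.4% vs 7.2% |
| 2.5 | 0.10 vs 1.10 | 3% vs 34% | 0.9% vs 10% | 0.4% vs 5.2% |

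Worked case, SE 1.5 and d = 5:
- M = 5: c = 5 − 2.94 = 2.06, and Φ((2.06 − 5)/1.5) = Φ(−1.96) = 2.5%.
- M = 6: c = min(2.94, 3.06) = 2.94, and Φ((2.94 − 5)/1.5) = Φ(−1.37) = 8.5%.
- The second term is negligible in both.

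**The four categories.** These carry no significance condition, so the label can change at any SE. For example, an estimate of 4.5 with an upper limit of 5.5 is possible under an MCID of 5 and definitely not under 6.

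**The case against.** The best reply is that the 6 is a one-digit slip. It appears once and no rule is built on it. Every cut-off used to judge the SBP difference is 5: below 5 is unimportant (Primary outcome), and at least 5 is clinically significant and below 5 is equivalence (Statistical methods). The equivalence criterion also comes soon after the definition of 5 mmHg. This makes 5 the likelier intention, and a reader should not infer that the Statistical methods section itself operates a 6 mmHg rule. It does not settle the matter. The criterion names the MCID without a number, the section on statistical methods states that number as 6, and reference [33] is not at hand.

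A reader might also infer that a 6 mmHg margin inflates false equivalence several-fold at any precision. Using the CI condition alone, at a true difference of 5 and SE 1, the figures would be 2.5% against 17%. The protocol does not support that reading, because it also requires a non-significant comparison. With that condition both figures are 0.12%. Whether non-significance is a sound requirement for equivalence is a separate question, but it is the written rule.

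It is also true that no design quantity depends on the margin.

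**Conclusion.** The contradiction is real: two MCIDs from one citation, with a criterion that points to the MCID without saying which. Its reach is limited. Under the full written rule it changes the decision only for non-significant results with an upper 95% limit from 5 to just under 6 mmHg, which can occur only when the SE exceeds about 1.28 mmHg. In that range the larger margin roughly triples the chance of declaring equivalence at a true difference of 5 mmHg for SE 1.5 to 2, and it also raises the chance for identical products. The category labels under Fig. 4 are affected more widely.

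These sizes rest on assumed SEs, a normal approximation and a two-sided reading of the margin. The documents do not show what SE to expect, so they do not show how likely the affected range is. The textual conflict needs none of these assumptions.

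**What to change.** State one MCID in the Primary outcome section, the criteria to establish therapeutic equivalence, and the Statistical methods section, and write the number into the criterion itself. The internally consistent value is 5 mmHg: it stands in the primary outcome definition, it matches every cut-off applied to the SBP difference, and it is the stricter of the two. First confirm it against reference [33], then correct the 6 in Statistical methods to 5.

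The Trial status section reports all 33 patients enrolled, so the correction should be dated and recorded before the randomization codes are broken. The cost is one source check, one corrected figure and one number added to the criterion. Sample size, schedule and data collection do not change.

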**Methods:**

This is a hospital-based, randomized, partially blinded, three-cycle crossover trial in single patients, comparing a locally produced version of enalapril with enalapril imported from Europe. Patients involved in this trial are not blinded, as there is no local facility to produce relatively small numbers of placebos or encapsulated drugs. To ensure blinding of study investigators and data analysts, study medications are prepared by an independent pharmacy unit using opaque medication packaging. The importance of maintaining blinding is also part of patient pre-trial education. Each N-of-1 trial will consist of three successive 14-day treatment pairs, each pair comprising 7 days of 5–20 mg local and 7 days of 5–20 mg imported enalapril taken once daily in the morning. The primary outcome will be the average difference in systolic blood pressure as measured by home blood pressure measurements.

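### The therapeutic-equivalence rule uses evening home SBP, a listed secondary outcome with 15 readings per period, although the primary outcome is home SBP with no time-of-day limit, planned on 30

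*Protocol article*

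**What the plan says.** All references are to the protocol article.

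- **Abstract, Methods:** "The primary outcome will be the average difference in systolic blood pressure as measured by home blood pressure measurements". No time of day is given.
- **Primary outcome:** equivalence is to be assessed on the change in mean seated SBP, again with no time of day. The word home does not appear in that sentence.
- **Using home BP measurement:** "The average systolic BP over 5 days is used to assess the effectiveness of treatment".
- **Criteria to establish therapeutic equivalence:** a confidence-limit criterion, to be met in two of three cycles, with no time of day.
- **Sample size estimation:** each individual trial is planned on "30 BP readings (twice a day, three times each time) taken from the last 5 days of each trial period". The number is taken from an earlier N-of-1 study, which found five days sufficient "provided that there are at least 30 readings in each 5-day trial period".
- **Secondary outcomes:** home SBP in the evening (12 h after intake) and home SBP in the morning (24 h after intake) are separate items.
- **Statistical methods:** "A mean change in evening SBP of" less than 5 mmHg between the two products, in at least two cycles, counts as equivalence.

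**The concern.** The sentence that decides the trial's main conclusion names a different variable from the one declared as primary, and that variable is on the secondary list. Two things follow if it is applied as written.

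First, the decision uses half of the readings on which each period was planned. Second, it looks only at about 12 h after intake. A product whose effect fades sooner could match the comparator in the evening and differ at 24 h, and the rule would not see it. The trial exists to detect differences between two formulations, and the Discussion says that patients could take the local product with confidence if none is found.

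With two definitions of the deciding variable in print, the document alone does not fix which one yields the verdict. That matters more here because patients are not blinded and take the readings themselves.

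**Working it through.** **1. Which variable is primary?** No sentence says that the primary outcome is the mean of morning and evening readings. It follows from three places.

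- The abstract, Primary outcome and Using home BP measurement set no time-of-day limit.
- The planned 30 readings need both times of day (step 2).
- The secondary list contains home diastolic pressure for morning and evening combined, clinic diastolic, clinic systolic, and home diastolic and home systolic for morning and evening separately. The one combination missing is home SBP over morning and evening together, which is what one expects if that is the primary outcome.

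**2. Reading counts.** Inputs: two occasions per day, three readings per occasion (Sample size estimation; Education and instruction for subjects), five usable days per period, six periods (Statistical methods).

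| | Morning + evening | Evening only |
|---|---|---|
| Per period | 2 x 3 x 5 = 30 | 1 x 3 x 5 = 15 |
| Per cycle (2 periods) | 60 | 30 |
| Per patient (6 periods) | 180 | 90 |

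The protocol's figure of 30 reproduces exactly, but only with both times of day. Evening only gives 15/30 = 50%.

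**3. Precision.** The protocol gives no variance components, so every SD below is an assumption. Variability is taken as equal in the morning and the evening. With day-level SD d, occasion-level SD o and reading-level SD r, the variance of a period mean is

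- both times: d²/5 + o²/10 + r²/30
- evening only: d²/5 + o²/5 + r²/15

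The day term is the same in both, because both use five days. The other two terms double.

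| d, o, r (mmHg) | SE, both | SE, evening | Ratio |
|---|---|---|---|
| 0, 0, 8 | 1.46 | 2.07 | 1.41 |
| 0, 6, 5 | 2.11 | 2.98 | 1.41 |
| 4, 5, 5 | 2.56 | 3.14 | 1.23 |
| 6, 3, 4 | 2.94 | 3.17 | 1.08 |
| 8, 0, 0 | 3.58 | 3.58 | 1.00 |

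The ratio runs from 1 (all variation between days) to √2 = 1.41 (none between days).

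For the difference within a cycle, SE = √[2(p² + o²/occasions + r²/readings)], where p is a period-level SD. With o = 6, r = 4 and no day-level term:

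- p = 0: √[2(36/10 + 16/30)] = 2.88 against √[2(36/5 + 16/15)] = 4.07, a rise of 41%.
- p = 2: √[2(4 + 36/10 + 16/30)] = 4.03 against √[2(4 + 36/5 + 16/15)] = 4.95, a rise of 23%.

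Both cases lie inside the 0% to 41% range.

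**4. Can the verdicts differ?** Let E and M be the true differences in the evening and the morning, both in the same direction. The evening rule asks whether E < 5. The combined mean asks whether (E + M)/2 < 5, that is, E + M < 10. The rules disagree whenever E < 5 and E + M ≥ 10, and also whenever E ≥ 5 and E + M < 10. As an assumed illustration, E = 3 and M = 9 pass the evening rule, since 3 < 5. The combined mean is (3 + 9)/2 = 6, which fails.

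**The case against.** The best defence is that the conflict turns on one word. The mixed model described in the same Statistical methods section refers to the three readings taken each morning and each evening, so the modelling does not appear to be limited to evenings. The 24 h readings are not lost to the trial either, because morning SBP is a listed secondary outcome. A statistical analysis plan that is not shown may name the variable, and the abstract says that the data analysts are blinded. All of this is fair, but none of it removes the conflict: the word stands in the decision rule, and no other part of the article overrides it.

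Some stronger readings should be resisted.

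- *The trial has two primary endpoints.* A reader might infer this, but the article declares one primary outcome and then decides equivalence on another variable.
- *The abstract and Primary outcome section define the outcome as morning plus evening.* They do not. That is an inference, though a well-supported one.
- *Precision falls by a fixed amount, such as 41%.* The article gives no SDs. If most variation is between days, the loss is close to nil.
- *A short-acting product would be missed.* The 3 and 9 mmHg example shows that the rules can disagree. Nothing in the article suggests that such a gap is likely.
- *The endpoint was, or will be, chosen after seeing results.* The text leaves that open but gives no sign of it.

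**Conclusion.** The point holds as an internal contradiction in the rule that decides the main conclusion. There is one primary outcome, home SBP without a time-of-day limit and by implication averaged over morning and evening. The equivalence rule replaces it with evening SBP, a secondary outcome.

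The certain consequences are 15 instead of 30 readings per period, against the protocol's own reliance on at least 30, and the exclusion of the 24 h readings from the decision. The conditional consequence is a 0% to 41% rise in SE, given equal variability at the two times of day and variance components of the kind shown. A different verdict under the two definitions is possible; its probability cannot be judged from the article. The rule should be corrected, because it is wrong as written and nothing else in the article resolves it.

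**What to change.** Under Statistical methods, replace evening SBP in the equivalence rule with: mean home SBP over all morning and evening readings of the last 5 days of each period. Use the same wording in the Primary outcome section, and keep evening and morning home SBP as the secondary outcomes already listed.

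The change needs no new data and no design change, but it is more than an edit of wording. Trial status reports all 33 patients enrolled and completion expected by 7 October 2017, and the article is dated 10 October 2017. Whether analysis had begun cannot be told from it. The choice should therefore be recorded as a dated decision made before unblinding. If that is no longer possible, both results should be reported and the discrepancy disclosed.

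This correction does not settle the rest of the rule. Two further conflicts are separate and must also be reconciled. The minimal clinically important difference is 6 mmHg in Statistical methods but 5 mmHg in Primary outcome and in the threshold itself. Equivalence is judged on a mean change in Statistical methods but on a confidence limit in the equivalence criteria.
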